#### Trial design

This pilot randomised, double-blind, placebo-controlled trial will recruit Parkinson’s disease patients. This is a prospective, exploratory, interventional study. Enrolled subjects will be equally randomised (1:1) in the placebo or intervention group.

## Methods: Participants, interventions, and outcomes

### Study setting

Patients will be enrolled at Azienda Ospedaliero-Universitaria Maggiore della Carità di Novara, where all visits will be scheduled. The setting of the study is a centre of care and research and an academic hospital.

### Eligibility criteria

All included patients will have a diagnosis of Parkinson’s disease with a disease duration between 2 and 5 years at baseline. Exclusion criteria for this study are listed in the following Table 2:

**Table 2 Tab2:** Exclusion criteria

**Condition**	**Exclusion criteria**
Present disease or disease history	Autoimmune disease Inflammatory bowel diseases Past major abdominal or pelvic surgery
Therapy	Immune-modulating or immunosuppressive Antibiotics therapy up to three months before enrolment
Feeding-related conditions	Usage of tube feeding Known or suspected allergy to any treatment or placebo component
Cognitive impairment	Known and established cognitive decline Any comorbidity preventing reliable completion of trial assessments
Parkinson’s symptoms	Motor fluctuations

Patients will be required to report any proposed modification in their medical therapy. Patients who will need substantial changes in antiparkinsonian therapy will be dropped from the trial. The use of laxative or prokinetic drugs will be recorded and is not an exclusion criterion per se, but the introduction of these medications or posology variations should be avoided during the trial.

Since the trial is primarily aimed at confirming the immunomodulating properties of probiotic treatment, any intercurrent and symptomatic infections, inflammatory episodes, or other medical conditions will be recorded. Evaluation by clinical staff for potential patient dropout will be based on the severity and temporal proximity of the event to scheduled visits and blood withdrawal. All participants will be advised to maintain a constant dietary intake and a regular physical activity during the trial. A daily report including quality of life aspects will be requested and evaluated using appropriate clinical scales. Informed consent will be obtained by clinicians after the eligibility assessment and during the first visit. All subjects or their legal representatives will be given all relevant information about the study structure and objectives. Additional consent will be requested for the use of collected data and biological specimens in ancillary studies.

#### Interventions

This is a placebo-controlled trial. The intervention group will be treated with a daily dose of probiotics, while the control group will be given identical packages containing maltodextrin only, used as a bulking agent in the probiotics’ formulation for the intervention group. In this pilot study, our aim is to assess the potential of probiotics therapy to modify the peripheral immune system profile and function in a cohort of PD subjects. In this pilot trial, the potential immunomodulating effects of probiotics will be tested. Placebo treatment was chosen as a comparator for this new approach to immunomodulation in PD.

During the enrolment visit, the medical and neurological examination will assess the need for immediate variations in medical therapy for each participant. Within 2 weeks, any therapy modification will be completed, and a baseline visit will be scheduled.

During the baseline visit (T0), physical and neurological examinations will be repeated to confirm the subject’s conditions and persistence of inclusion criteria, a baseline blood withdrawal will be performed, and all clinical evaluation scales will be completed to set baseline scores. Each participant, after the subscription of an appropriate informed consent, will be randomised and given a treatment box, containing single-dose sachets with 2.7g of powder of the allocated formulation. Patients will be instructed to take daily doses at home every morning before breakfast for 12 weeks, mixing the content of one sachet in about 125 ml of fresh water or other cold, non-carbonated drink. Participants will be instructed to keep unused or empty packaging for recollection and compliance evaluation.

Product compositions per dose (1 sachet, 2.7g) for the treatment and placebo compounds are listed in the following Table 3.

**Table 3 Tab3:** Treatment and placebo composition

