**Treatment composition**	
**Component**	**Quantity**
Bifidobacterium animalis subsp. lactis BS01	≥ 1 x 10^9^ CFU
Bifidobacterium longum 03	≥ 1 x 10^9^ CFU
Bifidobacterium adolescentis BA02	≥ 1 x 10^9^ CFU
Fructo-oligosaccharides FOS	2500 mg
Maltodextrin	q.s.

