## Discussion

The involvement of the immune system in the development and progression of Parkinson’s disease makes it a promising target for a disease-modifying therapy. This clinical trial will test the ability of probiotics therapy in modulating the peripheral immune system, which in turn is expected to have beneficial effects on disease progression and patients’ quality of life. If this trial shows a potential beneficial role of probiotics in immunomodulating peripheral immunity in PD patients, a trial with a larger cohort could be designed and disease progression could be monitored over a longer period to assess the disease-modifying potential of this intervention.

The possibility to use probiotics as adjuvant therapy in Parkinson’s disease could also help in reducing necessary drugs for the treatment of disease-related symptoms such as laxatives, prokinetics, and others (with a final reduction of individual therapy undesired effects and costs). The results of this study will also point further research in a disease-modifying direction. If further research shows a potential disease-modifying effect of probiotics, treatment could be proposed to all PD patients without any specific risks and increasing the quality of life in these patients.

In our mono-centric setting and considering rigorous exclusion criteria, one possible problem will be the recruitment of a large enough number of subjects. Enrolment will therefore be proposed to all eligible subjects by clinical neurologists during routine visits and given their recorded consent to receive information about ongoing research and recruiting trials. This will help in reaching the maximum number of possible participants, while ensuring strict adherence to inclusion/exclusion criteria, since participation will be only proposed to eligible patients by their neurologist and after a thorough medical evaluation.

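### The active sachet combines three Bifidobacterium strains with 2500 mg FOS and the placebo has neither, so the trial estimates the combined product, not probiotics alone as its aims and Discussion say

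*Protocol article*

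**What the plan says.** All of this comes from the protocol article.

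- **Product.** Interventions describes "single-dose sachets with 2.7g of powder of the allocated formulation". Table 3 lists the active sachet as three strains (for example "Bifidobacterium longum 03"), each at no fewer than 1 x 10^9 CFU, together with "Fructo-oligosaccharides FOS" at 2500 mg and maltodextrin as needed to fill.
- **Comparator.** Interventions states that "the control group will be given identical packages containing maltodextrin only, used as a bulking agent". The placebo part of Table 3 agrees: maltodextrin is its only entry.
- **What is to be tested.** Interventions: "In this pilot trial, the potential immunomodulating effects of probiotics will be tested". Eligibility criteria: "the trial is primarily aimed at confirming the immunomodulating properties of probiotic treatment". Discussion: "This clinical trial will test the ability of probiotics therapy in modulating the peripheral immune system". The Objectives section also speaks of the immune-modulating potential of probiotics.
- **Link to laboratory work.** Primary feasibility outcomes recalls the group's in vitro finding on ROS and cytokines with probiotics and proposes to check whether it holds in vivo. Sample size draws on the in vitro effects of the tested strains.

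FOS appears only in Table 3. The article does not call it inert, provides no arm or placebo matched on FOS, and does not say that the effect of interest is that of strains and FOS together.

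**The concern.** The stated question and the comparison made do not match. The question is about probiotics. The comparison changes two things at once: the strains are added, and so is a daily 2500 mg of FOS for 12 weeks. A difference between arms could come from either or from the two acting together, and the trial has no data to tell these apart.

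The protocol's own reasoning makes this hard to set aside without argument. Its proposed mechanism runs through the gut microbiota. It asks participants to keep their diet constant, limits the recruitment period to avoid seasonal changes in diet, and collects several constipation and bowel scales. An oral carbohydrate given to one arm only is the kind of difference that the protocol elsewhere tries to control.

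At stake is the wording of the conclusion. The pilot is meant to choose outcomes and supply sample-size data for a main trial, and the Discussion looks ahead to probiotics as adjuvant therapy. A result for the combination, reported as a result for the bacteria, would carry the wrong label into both.

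**Working it through.** **Inputs (Interventions and Table 3).** Sachet mass is 2.7 g = 2700 mg. FOS is 2500 mg in the active sachet and 0 mg in the placebo. There are two arms, allocated 1:1 (Trial design).

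**Composition.**
- FOS share of the active sachet: 2500 / 2700 = 0.926, or 92.6%.
- Remainder for strains and maltodextrin together: 2700 − 2500 = 200 mg at most, or 7.4%.
- FOS share of the placebo: 0%.

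**What two arms identify.** Let μ(s,f) be the mean outcome with strains present or absent (s = 1 or 0) and FOS present or absent (f = 1 or 0), taking maltodextrin as the reference. The trial observes μ(1,1) and μ(0,0) only. The between-arm contrast is

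μ(1,1) − μ(0,0) = [μ(1,0) − μ(0,0)] + [μ(0,1) − μ(0,0)] + interaction,

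where the interaction is μ(1,1) − μ(1,0) − μ(0,1) + μ(0,0). That is one estimable quantity and three unknown parts. The first bracket, the effect of the strains alone, would need μ(1,0) or, given FOS, μ(0,1). Neither cell exists. The left-hand side is estimated without bias from the product difference, because randomisation protects it.

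The strains could be credited with the whole contrast only if the FOS term and the interaction were both zero. The protocol neither states nor argues that.

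**The plan's own figure.** Sample size gives 80 subjects and power above 80% at a 0.05 threshold. No effect size or standard deviation is printed, so this can be neither reproduced nor refuted. The present point does not depend on it.

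**Which objectives depend on separating the components.**

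| Objective | Affected? |
|---|---|
| Recruitment, acceptance and dropout rates | No |
| Comparison of the whole product with maltodextrin | No |
| Choosing outcomes and estimating sample size for a main trial of the same product | No, if labelled as such |
| Attributing an immune effect to probiotics as bacteria | Yes |
| Treating the result as in vivo support for the in vitro probiotic findings | Yes |

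**The case against.** The best reply is that the protocol uses the word probiotics for the product, prints the full composition openly, and nowhere claims to isolate the strains from FOS. On that reading the randomised comparison is sound and only the label is loose. Most of this stands: the comparison is valid for the product, and the feasibility aims do not need the components separated. It does not dispose of the point. The aims are worded as confirming properties of probiotic treatment and are tied to laboratory findings described in terms of probiotic strains. Nothing tells the reader that the inference covers a combination.

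Several stronger readings are tempting, and the documents do not support them.

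- *The trial is invalid, or can say nothing about its intervention.* It can, for the combined product.
- *FOS must drive the result because it is 92.6% of the weight.* Weight does not measure biological contribution, and the strains are specified in CFU. Nor should the strains' share be given as a range from 0% to 100%: that presumes additive effects in one direction, and the documents give no basis for it.
- *FOS is known to be active, or unblinds the active arm through gut symptoms.* The article gives no information on its activity and no figure on unblinding. It describes identical packages and blinding of participants, care providers, assessors and analysts.
- *Calling maltodextrin the bulking agent contradicts Table 3.* It does not. A filler added as needed may be a small remainder.
- *The in vitro preparations contained no FOS.* The article's short summary mentions none, but that does not show how they were made up.

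**Conclusion.** The concern holds as a fault of attribution, not of the randomised comparison. The design identifies the joint effect of three strains plus 2500 mg FOS against maltodextrin. It does not identify the effect of the strains. The protocol's aims, its link to the in vitro work and its Discussion assign the effect to probiotics without that limit, so a positive result reported as planned would claim more than the design can support.

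The size can be stated only as composition: FOS is 92.6% of the active sachet by weight and 0% of the placebo. How much of any effect comes from each component is not identified, and no estimate is offered.

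The conclusion assumes that Table 3 is the product actually supplied and that FOS has not been shown to be inert for these outcomes. If the full protocol makes that second case, the point weakens accordingly. The matter is not one of detail left to an analysis plan: the composition and the attribution are both printed here, and they do not match.

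**What to change.** Leave the product, patients and visits as they are. Recruitment stands at 40 of at least 80 (40/80 = 50%), so a change of wording is the practical course.

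1. In the aims, outcomes and Discussion, describe the intervention as the combined product (three Bifidobacterium strains plus FOS) and state that the contrast is this combination against maltodextrin.
2. Say explicitly that the components cannot be separated.
3. Narrow the aim in Eligibility criteria and the sentence in Primary feasibility outcomes about checking the in vitro findings in vivo, so that neither attributes an effect to the bacteria alone.
4. Note that outcomes selected and effect sizes estimated for the main trial apply to the combined product only.

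The cost is a few sentences and a narrower permitted conclusion. No recruitment, visit or analysis changes.

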#### Objectives

The aim of this pilot study protocol is to assess the feasibility of a randomised controlled trial to assess the effects of a 3-month probiotics therapy in a cohort of Parkinson’s disease patients. Specific feasibility objectives will be assessed to define the feasibility of the proposed clinical trial, including recruitment, acceptance and dropout rate, and outcome identification, as listed in the following Table 1.

**Table 1 Tab1:** Feasibility objectives

**Objective**	**Description**
Recruitment rate	The number of identified eligible subjects in a given amount of time, at the proposed clinical setting.
Acceptance rate	The fraction of identified eligible subjects who will be willing to participate in the proposed clinical trial.
Dropout rate and safety	Dropout rate will be reported as the fraction of enrolled subjects who will be dropped from the study for any reason. Reported reasons for subject drop-out will be recorded and analysed to confirm safety for both the treatment and placebo administration to enrolled subjects.
Primary outcome identification and sample size estimate	The primary outcome for the future main clinical trial will be identified among significant immune profile changes detected in the pilot trial. Data from the pilot trial will also be used to estimate an appropriate sample size for the main trial.
Secondary outcomes identification	Collected data in the pilot trial will be used to identify promising secondary outcome measures.

Data collected during this pilot study will include the following assessments to evaluate possible outcome measures for the definitive randomised controlled trial:1) Cytokines production (IFN-γ, TNF-α, IL-4, IL-10), as already tested in vitro, to confirm the immune-modulating potential of probiotics.2) Assessment of CD4+ and CD8+ T naïve/memory cells, CD4+ T helper subsets, CD4+ regulatory T cells, monocytes, and NK cells to test the immunomodulating effects of probiotics administration on the immune profile.3) Monitoring of motor and non-motor symptoms of PD, including gut function, and subjective quality of life during the trial period.

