**Placebo composition**	
**Component**	**Quantity**
Maltodextrin	q.s.

Follow-up visits will be scheduled at 6 weeks after T0 (T1) and at 12 weeks after T0 (T2). At T1, physical and neurological examination will be repeated, and all clinical scales administered again, except for Bristol Stool Form Chart and MOCA. At T2, all assessments performed at T0 will be carried out again, including blood withdrawal.

Participants will be advised to report any suspected adverse reaction and new or worsening symptoms. Every report will be recorded, and a thorough evaluation will be performed by neurologists in the clinical staff in collaboration with the subject’s primary care doctor. Feedback will be provided to the participant as well as indications on continuing or stopping treatment administration. In accordance with the Declaration of Helsinki by the World Medical Association, every participant can freely request to be removed from the study at any moment. All participants will be requested to record daily treatment usage and keep empty packaging or unused doses for recollection after the trial completion. One courtesy call will be scheduled during treatment to reduce compliance issues. The use of immunomodulating drugs or antibiotic therapy is an exclusion criterion and patients starting such therapy during the trial period will be dropped from the study. Dose adjustments in antiparkinsonian therapy are permitted but should be avoided and substantial modifications to said therapies will cause dropping out from the study.

Every participant will be evaluated at enrolment by a clinical neurologist, who will assess needed adjustments in antiparkinsonian therapy that will be completed within two weeks from enrolment and before treatment administration to minimise the need for medical therapy modifications during the trial. The use of laxative or prokinetic drugs will be recorded and is not an exclusion criterion per se, but the introduction of these medications or posology variations should be avoided during the trial.

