### Outcomes

#### Primary feasibility outcomes

To assess the feasibility of the proposed clinical trial, we defined different feasibility objectives, as previously listed in Table 1.

More in detail, we will evaluate the potential recruitment rate for the clinical trial by recording the number of eligible outpatients who scheduled a neurological examination in the proposed clinical setting during the pilot trial. The acceptance rate will also be evaluated, by recording the fraction of identified eligible subjects who will be willing to participate in the proposed clinical trial. Both assessments together will allow for an initial estimate of the needed duration for the main clinical trial, once an appropriate sample size will be defined based on the pilot trial results. During the pilot trial, the dropout rate will also be recorded to adjust the predicted trial duration based on the fraction of dropped-out subjects during the trial period.

Reported reasons for subject drop-out will also be recorded and further analysed to confirm the safety of both the treatment and placebo administration to enrolled subjects. Collected data during the pilot trial will be analysed to assess whether a significant variation in any recorded parameter will occur between the two trial branches. This will allow to accordingly select one or more appropriate primary outcomes for the main trial, among collected immune profile data. Secondary outcomes for the main trial will be selected in the same way, among parameters who will show a remarkable variation.

More in detail, in our previous in vitro study (Magistrelli et al., 2019), we demonstrated that probiotics modulate ROS and cytokine production by driving an anti-inflammatory profile. Therefore, we will test whether these properties are confirmed in vivo. Particularly, in our study, we want to analyse whether probiotics may modulate cytokines production, such as IFN-γ, TNF-α, IL-4, IL-10, and ROS production.

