### Sample size

The design of this pilot study is explorative and equally randomised to treatment with probiotics or placebo. Due to the exploratory nature of the proposed study, a formal sample size calculation is not strictly required [18]. In our precedent in vitro study, statistically significant results were found in a small cohort of 40 PD patients for all tested probiotic strains, with a global reduction in proinflammatory cytokines production and an increase in anti-inflammatory cytokines. Doubling this sample size, with at least 80 specimens to be collected at both T0 and T2, will allow us to correctly evaluate the feasibility of the future main study.

We thus used data from the said study to estimate sample sizes for the in vitro effect of all tested probiotic strains and a sample size of 80 subjects allows for the determination of most tested cytokines variations with an expected power greater than 80%, setting our threshold for statistical significance at 0.05.

As previously stated, the drop-out rate of this pilot study will also be recorded and used to determine an appropriate sample size increase for the main study.

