### Statistical methods

#### Statistical methods for outcome evaluation

To assess the main trial feasibility, the drop-out rate will be reported as the absolute number and percentage of total participants for both the intervention and placebo arms and will be accounted for when assessing an appropriate sample size for the main study. Feasibility will also be evaluated by recording all drop-out reasons and accordingly estimating an increase of the foreseen sample size.

Collected results will be reported as mean ± standard deviation (SD) of the mean, or median ± 25th and 75th percentile, as appropriate, and *n*, with *n* indicating the number of observations. The normality of data distribution will be analysed by means of D’Agostino-Pearson omnibus normality test. Mann–Whitney *U* test, Wilcoxon test, and Kruskal-Wallis tests will be used to assess differences in the distribution of non-parametric data. Paired and unpaired *t* tests will be used, as appropriate, to compare means and standard deviations for parametric data in the two treatment groups. Wilcoxon signed ranks test will be used to compare measures taken at T0 with the corresponding measures at T1 and T2 in the assessment of primary and secondary outcomes. When appropriate, efficacy outcomes will be reported as estimates with 95% confidence intervals. Statistical significance for correlations will be set at *p*<0.05. Commercial software (GraphPad Prism version 9.3.0 for Windows, GraphPad Software, San Diego, CA, USA, www.graphpad.com) will be used for data analyses and graph plotting.

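### Intake of the daily sachets is recorded, but the plan has no stated plan to report adherence as a feasibility outcome, and one rule would restrict any summary to adherent patients

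*Protocol article*

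**What the plan says.** The regimen is set out under Interventions: "Patients will be instructed to take daily doses at home every morning before breakfast for 12 weeks". The same section provides for intake to be checked: "Participants will be instructed to keep unused or empty packaging for recollection and compliance evaluation". The text after the product composition tables adds a daily record: "All participants will be requested to record daily treatment usage and keep empty packaging or unused doses for recollection after the trial completion". It also schedules one call to limit compliance problems, and the Discussion says participants will be contacted so that adherence can be assessed.

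The feasibility objectives are given as a list, "including recruitment, acceptance and dropout rate, and outcome identification, as listed in the following Table 1". The Primary feasibility outcomes section adopts it: "we defined different feasibility objectives, as previously listed in Table 1". Table 1 defines drop-out as follows: "Dropout rate will be reported as the fraction of enrolled subjects who will be dropped from the study for any reason". Under Statistical methods for outcome evaluation, the feasibility statistic with a reporting rule is drop-out: "the drop-out rate will be reported as the absolute number and percentage of total participants for both the intervention and placebo arms", together with its reasons. The Sample size section carries one feasibility quantity forward: "the drop-out rate of this pilot study will also be recorded and used to determine an appropriate sample size increase for the main study".

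Two further statements bear on which data exist. The Interim analyses section takes non-adherent patients and drop-outs out of the study and adds that no data on them are gathered. The section on participant retention says that what was gathered before a patient left is retained and may be analysed.

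**The concern.** For a product that patients take unsupervised at home, whether they actually take it is a basic feasibility question. The plan gathers the raw material to answer it in three ways, but its list of feasibility outcomes does not name the answer as a result.

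Drop-out cannot stand in for it. Drop-out counts who left. It does not show how many sachets were taken by those who stayed, or whether partial intake differed between the arms.

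The exclusion rule makes this worse. If non-adherent patients are removed and their data not gathered, any compliance figure describes a group chosen because it complied. The same holds for the immune changes that the pilot will use to choose outcomes and size the main trial.

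**Working it through.** The plan states no adherence figure, so there is nothing of its own to reproduce on this point. Its sample size of 80 cannot be reproduced either, because no effect size or standard deviation is given, but this point does not depend on it.

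**Step 1. Collected against reported.**

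| Item | Collected? | Named as a feasibility result? |
|---|---|---|
| Eligible patients over time | Yes | Yes (Table 1) |
| Acceptance | Yes | Yes (Table 1) |
| Drop-out and reasons | Yes | Yes (Table 1; Statistical methods; Sample size) |
| Sachets returned, daily record, adherence contact | Yes (Interventions and following text; Discussion) | No |

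**Step 2. Scheduled intake.** One sachet a day for 12 weeks is 12 × 7 = 84 sachets per patient.

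**Step 3. What drop-out reveals about intake.** Take two hypothetical pilots with no drop-outs. In one every patient takes 84 of 84 sachets. In the other every patient takes 70%, which is 0.70 × 84 = 58.8, or about 59. Both report a drop-out rate of 0%, so the listed outcomes do not separate them.

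**Step 4. What the exclusion rule does to a compliance summary.** Suppose, as an assumption, that 16 of 80 randomised patients are non-adherent. Among all randomised patients the adherent share is 64/80 = 80%. If the 16 are removed and their data not kept, the remaining share is 64/64 = 100% by construction. The 16 would still count as drop-outs (16/80 = 20%) with a recorded reason, but how much they took would be lost.

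**Step 5. What the pilot could estimate.** The Wilson 95% interval for a proportion p from n patients, with z = 1.96, is

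[p + z²/(2n) ± z·√(p(1−p)/n + z²/(4n²))] / (1 + z²/n).

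- n = 80, p = 0.80: centre (0.80 + 0.0240)/1.0480 = 0.786; half-width 1.96 × √(0.00200 + 0.00015)/1.0480 = 0.087; interval 0.700 to 0.873.
- n = 40 (one arm), p = 0.80: centre (0.80 + 0.0480)/1.0960 = 0.774; half-width 1.96 × √(0.00400 + 0.00060)/1.0960 = 0.121; interval 0.652 to 0.895.

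The 80% is an assumption. At n = 80, an observed 70% would give 0.592 to 0.789 and an observed 90% would give 0.815 to 0.948. That is precise enough to tell a workable regimen from a poorly followed one overall, and less so within an arm.

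**Step 6. The two data statements.** One section says data on non-adherent patients and drop-outs are not gathered. Another says data gathered before drop-out are retained and may be analysed. Both cannot govern the intake record of a patient who leaves in, say, week 8.

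**The case against.** The plan does foresee a compliance evaluation, and its statistical section has a general rule for summarising collected results. A named compliance table is the sort of detail an article may leave to the full protocol. A reader might infer that adherence will go unreported. The documents do not support that, only that reporting it as a feasibility outcome is not stated. What survives is that the article does fix its feasibility outcomes as an explicit list, repeats it, and leaves adherence off. Which outcomes a feasibility pilot has is protocol content.

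Non-adherence that leads to removal would not be invisible either. Drop-out covers removal for any reason, reasons are recorded, and rates are given for both arms. That stands. What stays unreported is partial intake among patients who remain, and the amount taken by those removed.

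A stronger reading is also tempting: that the main trial will be undersized by a known factor. If effect is proportional to the share a of sachets taken, the required size grows as 1/a²: 1.23 times at 90%, 1.56 at 80%, 2.04 at 70% and 2.78 at 60%. These multipliers do not measure a shortfall here. The main trial is to be sized from the pilot's own data, and partial intake among retained patients is already in the effect observed there, so applying 1/a² would count the dilution twice. For patients removed as non-adherent, the planned drop-out increase covers them if the main trial keeps the same exclusion rule. A gap would open only if the main trial retained such patients or its adherence differed from the pilot's, and the documents say neither.

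**Conclusion.** The point holds in a limited form. The pilot collects intake data but has no stated plan to report adherence as a feasibility outcome. The rule in the Interim analyses section, read literally, would confine any compliance summary, and the effect carried into main-trial sizing, to patients selected for adherence. That rule conflicts with the retention section.

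No size can be put on the consequence for the main trial, since the documents give neither an intake figure nor the main trial's handling of non-adherent patients. What can be sized is the information forgone: with 80 patients, an adherent share near 80% would be known to within about 70% to 87%, and to within about 65% to 90% in an arm of 40. These intervals assume that intake data are available for all randomised patients. The point is worth acting on because it bears directly on the pilot's stated aim and the data are largely being gathered already.

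**What to change.** - Add an adherence row to Table 1, and carry it into the Primary feasibility outcomes and Statistical methods sections: sachets taken out of the 84 scheduled, from returned packaging and the daily record, by arm, with a 95% confidence interval.
- Report it for all randomised patients, using intake recorded up to drop-out for those who leave.
- Reconcile the statement in the Interim analyses section with the one in the retention section, so that these data are kept. This concerns the data only. Whether a patient continues in the study is for the trial team.
- Consider adherence alongside drop-out when planning the main trial, and state whether the pilot effect used for sizing comes from all randomised patients or only from those who adhered.

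The cost is one more descriptive table and a clarification of the data rule, with no new visits or measurements. Returns may be incomplete for patients who drop out and for those among the 40 already recruited at the time of writing, because packaging is collected only after completion. The number with missing intake data should be shown. The feasibility picture may look less favourable. No interim analysis is planned, so the change can still be made before results are known.
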